## Discussion

### Anticipated Findings

This protocol aims to measure the impact of an MD adapted to the Mexican population on cardiovascular risk indicators, such as glucose, lipid profile, body weight, and blood pressure in patients with OSA. In addition, as secondary objectives we seek to evaluate the effect of the MD on sleep quality and quality of life, as well as the improvement in diet quality.

There is enough evidence on the cardioprotective effect of MD, which is not only proven in European countries: there are clinical trials evaluating MD adapted to the Chilean population suffering metabolic syndrome [25]. It has been proven that interventions aimed at lifestyle improve AHI, showing a reduction by –4.55 events per hour and improving weight and BMI among patients with OSA; however, no effect on sleep and life quality has been found [26]. Despite the ample evidence supporting the cardioprotective benefits of the MD, its evaluation has been predominantly focused on patients with obesity, diabetes, and, to a lesser extent, patients with OSA. The impact of adapting the MD diet with food in Mexico has been examined to a lesser extent.

The relationship between cardiometabolic risk factors and sleep duration has been previously reported in 47 patients with OSA in a rural community in the southeastern United States. The authors reported that shorter sleep duration was associated with an increased risk of hypertension, obesity, and impaired metabolic indicators. [27]. The results of this study suggest that an MD intervention with a preference for fruit, vegetables, high-fiber cereals, and white meat protein may improve cardiometabolic indicators.

Obesity and related diseases, like diabetes, hypertension, and dyslipidemia, represent a greater risk for patients with OSA. Then, CPAP treatment combined with weight loss is an effective strategy to reduce cardiovascular risk [28]. Adaptation to the patient's tastes, customs, and budget is necessary to improve adherence to MD. This study seeks to adequate MD to the Mexican diet to make it accessible, since typical MD includes foods considered high-priced for the population receiving care at public health care institutions in Mexico.

Furthermore, improvement in cardiometabolic indicators, such as glucose, lipid profile, and weight loss, is likely. Patients are expected to lose 5%-10% of their initial body weight, as reported by similar interventions [12].

Sleep quality in patients with OSA could improve after the proposed nutritional intervention, while the number of obstructive respiratory events could be reduced given that the size of the oropharyngeal lumen is reduced because of body fat loss [29]. Besides the reduction in obesity, the diet is expected to improve fasting glucose, arterial blood pressure, and dyslipidemia in patients with OSA taking part in the trial. We also expect this trial to positively affect daytime drowsiness in the patients and improve their quality of life. This clinical trial would be one of the few conducted in Mexico with patients with OSA where the implementation of low-cost strategies aims at improving cardiometabolic indicators and quality of life of those patients with OSA who receive care at public health care institutions in Mexico.

Among the limitations of the present study, adherence to the MD could be found; therefore, it is relevant to adapt the diet to the economic resources, habits, and customs, which allows an adequate adherence to the MD. A personalized diet and a timely follow-up will be provided to reinforce adherence to the nutritional intervention. It has also been shown that the use of CPAP is limited in the population with OSA, since they do not consider it necessary for their condition or it is difficult to use it to sleep adequately [30]. One of the potential limitations of the study is the use of a self-reported tool to collect sleep quality information. There will be limitations to the generalizability of the effect of the intervention, as it will be a single-center study. In this sense, as one of the main variables is to measure the improvement in sleep quality, this could be improved with the use of CPAP, so its use will be recorded in the follow-up visits, to include it in the multivariate analysis.

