Weight loss in patients with OSA is directly proportional to reduced respiratory events measured by AHI. This was reported in 89 men with OSA who reduced body weight by 7%, fat by 19%, and visceral adipose tissue by 26%, in addition to changes in lifestyle. As a result, OSA was reduced by 15% and 45% of the patients did not need CPAP anymore [8]. Evidence indicates the Mediterranean diet (MD) is widely cardioprotective and contributes to lowering cardiovascular risk and even death [9-11]. The PREDIMED study reported that an MD, mostly consisting of fruit, vegetables, white meat, and dried fruit or olive oil, reduced cardiovascular event symptoms in patients compared to those who followed a controlled diet. The MIMOSA (Mediterranean Diet/Lifestyle Intervention in Obstructive Sleep Apnea) study conducted with 187 adults with OSA showed that an intervention with MD or Mediterranean style had a better effect on improving cardiometabolic indicators than a standard diet (SD) [12]. In addition, the authors report a greater reduction in metabolic syndrome with MD in patients with OSA, even when adjusting fluctuations in body weight as compared with a Mediterranean style or an SD [13,14]. Fewer insomnia episodes have been linked to greater adherence to MD in patients with OSA and insomnia [15]. Although it has been shown to be cardioprotective and improve metabolic indicators, MD must be adapted to other countries. In Mexico, there is scarce evidence on the modification of MD to the Mexican diet and its cardiometabolic effect in patients with OSA. Therefore, the aim of this study is to evaluate the effect of a MD adapted to Mexican eating habits versus a standard nutritional treatment on metabolic risk indicators in patients with OSA.

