**Figure 2 figure2:**
[figure not shown]
Follow-Up and Study Procedures.

Follow-up will continue after 3, 6, and 12 months for MD and 6 and 12 months for SD diet participants, who will attend a consultation with a nutritionist and medical team. In order to measure the adherence to the diet in both groups, the patients will register the 3 days before their clinical visit, 2 registrations from Monday to Friday, and one on weekends. At each visit, nutritional guidelines will be given to improve adherence to the nutritional intervention. The study follow-up is shown in Table 2.

**Table 2 table2:** Study follow-up and procedure in patients with obstructive sleep apnea in both groups.

Time collection	Baseline	3 months	6 months	12 months
Collection of sociodemographic data	MD^a^ and SD^b^	—^c^	—	—
Medical history	MD and SD	—	—	—
Medical evaluation	MD and SD	—	MD and SD	MD and SD
Biochemical data	MD and SD	—	—	MD and SD
Arterial blood pressure and Anthropometric and body composition measurements	MD and SD	MD	MD and SD	MD and SD
Sleepiness with Epworth sleepiness scale	MD and SD	MD and SD	MD and SD	MD and SD
Quality of life with Quebec Sleep Questionnaire (QSQ)	MD and SD	—	—	MD and SD
Physical activity with IPAQ^d^ Questionnaire	MD and SD	—	MD and SD	MD and SD
Adherence to the diet intervention with records of the previous 3 days	MD and SD	MD	MD and SD	MD and SD
Adherence to the diet intervention with MEDAS^e^ Questionnaire	MD and SD	MD	MD and SD	MD and SD
Phone call follow-up	—	SD	—	—

^a^MD: Mediterranean diet.

^b^SD: standard diet.

^c^Not applicable.

^d^IPAQ: International Physical Activity Questionnaire.

^e^MEDAS: 14-point Mediterranean diet adherence screener questionnaire.

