### Statistical Analysis

The statistical analysis of the data will be carried out using SPSS (version 27; IBM Corp). The study population will be described using the background, clinical, and pathological variables to characterize the sample of participants with OSA. The Kolmogorov–Smirnov test will be used to identify the distribution of quantitative variables. For variables with normal distribution measures of central tendency and dispersion will be estimated. For variables with a free distribution mean and IQR will be used. Measures of frequency and percentages will be used for sociodemographic and clinical qualitative variables, as well as those of patient proportion with and without glycemic control, and with and without cognitive impairment. A chi-square test will be used to compare the effect of MD versus SD on parameters of control and uncontrol of metabolic risk indicators. Depending on the data distribution, a Student *t* test will be used to compare quantitative variables with parametric distribution between groups, and a Mann-Whitney *U* test will be conducted for free-distribution variables. A multivariate logistic regression analysis will be performed, including the achievement of metabolic indicator control goals, sleep quality, and quality of life as outcome variables. This analysis will be adjusted for other variables that may be statistically significant in the bivariate analysis, such as sex, age, and comorbidities, among others. Statistically significant differences between groups will be considered when the value of *P*<.05.

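### Follow-up CPAP use is a planned covariate in the multivariable model; if the diet changes that use, the adjusted coefficient no longer estimates the total effect of assignment to the diet

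*Protocol article*

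**What the plan says.** The Statistical Analysis section defines the model: "A multivariate logistic regression analysis will be performed, including the achievement of metabolic indicator control goals, sleep quality, and quality of life as outcome variables". Its covariate rule is "This analysis will be adjusted for other variables that may be statistically significant in the bivariate analysis, such as sex, age, and comorbidities, among others". CPAP is not named there, and nothing limits covariates to values taken before randomisation.

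CPAP enters through the limitations paragraph under Anticipated Findings. The reason given is that, "as one of the main variables is to measure the improvement in sleep quality, this could be improved with the use of CPAP", and the consequence drawn is "so its use will be recorded in the follow-up visits, to include it in the multivariate analysis". The covariate is therefore use during follow-up, and the sentence does not confine it to the sleep-quality model.

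Other relevant places:
- Textbox 1 makes CPAP use an inclusion criterion, so every patient is a user at entry.
- The Introduction cites a weight-loss and lifestyle study of 89 men in which "OSA was reduced by 15% and 45% of the patients did not need CPAP anymore".
- Anticipated Findings expects 5% to 10% weight loss and says that "the number of obstructive respiratory events could be reduced". It also gives perceived lack of need as one reason patients leave CPAP unused.
- Table 2 has no row for CPAP use. It does have a medical evaluation at baseline, 6 and 12 months in both arms.

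**The concern.** The protocol treats follow-up CPAP use as a confounder. In a randomised comparison, differences in CPAP use that exist before allocation are balanced in expectation. A difference between arms that appears later may be a result of the diet.

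Conditioning on such a variable does two things. It removes whatever part of the diet's effect runs through CPAP use. It also opens a path through factors that drive both CPAP use and outcome, such as motivation or general adherence.

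The regression is the only inferential analysis named in the Abstract, and the Results section expects group differences in it. A reader will probably take its coefficient as the effect of the diet. Nothing shown labels the CPAP-adjusted model exploratory or names a multivariable model without CPAP as the main one.

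**Working it through.** The plan gives no figure for this point, so there is none to reproduce. The sample size (49 per group before losses, from 58% versus 30% with weight loss) does not involve CPAP and is not affected.

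**Step 1. Is the covariate post-randomisation?** Yes. All patients use CPAP at entry (Textbox 1), so any contrast between users and non-users at a follow-up visit has developed since enrolment.

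**Step 2. Does the protocol give a path from diet to CPAP use?** It gives a plausible one. The sample size assumes a difference between arms in weight loss of 58% − 30% = 28 percentage points. The Introduction links weight loss to fewer respiratory events and to less need for CPAP. Anticipated Findings expects fewer obstructive events and says patients drop CPAP when they think it unnecessary.

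**Step 3. Does it give a path from CPAP use to outcome?** Yes for sleep quality; this is its stated reason for adjusting.

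**Step 4. What does adjustment then estimate?** All coefficients here are assumed. The model is linear, although the trial's is logistic, because a logistic coefficient also shifts when any prognostic covariate is added, and that would blur the comparison.

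Let T be the arm, c CPAP use (unit variance within arm) and U an unmeasured shared cause:

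- c = aT + 0.5U + error
- y = 0.5T + 0.4c + 0.3U + error

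The total effect is 0.5 + 0.4a and the direct effect is 0.5. Given T and c, the expected value of U is 0.5(c − aT). The adjusted coefficient of T is therefore 0.5 − 0.3 × 0.5 × a = 0.5 − 0.15a.

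| a (SD change in CPAP use) | Total | Direct | Adjusted |
|---|---|---|---|
| −0.25 | 0.40 | 0.50 | 0.54 |
| −0.50 | 0.30 | 0.50 | 0.58 |
| +0.50 | 0.70 | 0.50 | 0.43 |

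Adjusted minus total is −0.55a. Of this, −0.40a is the move from total to direct effect and −0.15a is bias from the shared cause. Under these values about 73% of the gap (0.40/0.55) is a change of estimand.

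**Step 5. Second check, CPAP as yes/no.** A simulation with 400,000 patients used logit P(CPAP) = 0.4 + aT + uU and y = 0.3T + bM + 0.5uU + error of unit variance, where M is CPAP use. The direct effect is 0.30 throughout.

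| Assumption | CPAP use, SD vs MD | Without CPAP in model | With CPAP in model |
|---|---|---|---|
| Diet does not change use (a = 0) | 58–60% in both | 0.30 | 0.30 |
| Use falls, b = 0.5, u = 0 | 60% vs 48% or 35% | 0.24 or 0.18 | 0.30 |
| Use falls, b = 0.5, u = 1 | 58% vs 48% or 38% | 0.25 or 0.20 | 0.35 or 0.39 |
| Use falls, b = 0, u = 1 | 58% vs 48% or 38% | 0.30 | 0.34 or 0.39 |

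The unadjusted column agrees with 0.30 + b × (difference in use). In the third row, for example, 0.30 + 0.5 × (0.380 − 0.581) = 0.20. With a shared cause, the adjusted figure matches neither the total nor the direct effect, even when CPAP has no effect on the outcome (last row).

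**The case against.** The strongest defence is that a difference between arms in CPAP use is not established. Both arms receive the same energy and macronutrient prescription, and the standard-diet arm also gets weight-loss guidance. The 45% comes from one cited study of 89 men, described without a comparator, and concerns need for CPAP, not use. Polysomnography is done once, so no scheduled test reassesses need. This stands to the extent that the bias is conditional: with no effect of diet on CPAP use, adjustment does no harm. It does not clear the plan, because the protocol expects the arms to differ in weight loss and says perceived need drives use.

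It can also be said that the aim is to separate the diet's effect from that of CPAP. That is a direct-effect question, but the protocol does not label it so, and a shared cause would bias that answer too.

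The reach is limited. The chi-square, t and Mann-Whitney comparisons do not use CPAP, so an unadjusted randomised comparison remains available.

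Three stronger readings are tempting and are not supported:
- *Baseline CPAP use is not collected.* The missing Table 2 row might suggest this. But use is checked at entry as an inclusion criterion, and the baseline questionnaire covers nonpharmacological treatments.
- *CPAP use will be recorded more often in the Mediterranean-diet arm.* The schedule reads "Follow-up will continue after 3, 6, and 12 months for MD and 6 and 12 months for SD diet participants", which makes this possible. The protocol does not say at which visits CPAP is recorded, however. The medical evaluation, a natural place for it, has the same timing in both arms, and the standard-diet arm has a telephone call at 3 months.
- *A main outcome is at stake.* The limitations paragraph calls sleep quality a main variable, but the Primary Outcomes section lists sleep quality and quality of life as secondary.

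**Conclusion.** The point holds in conditional form and for the multivariable logistic model only. If the diet changes CPAP use, the coefficient adjusted for follow-up CPAP use does not estimate the total effect of assignment, and shared causes can bias it as a direct effect. The protocol's own text makes this plausible but does not prove it.

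Neither size nor direction can be derived from the documents. A reader might take from the first table an error of +34% (0.54 against 0.40) or −39% (0.43 against 0.70). Those figures rest wholly on assumed coefficients in a linear model, and most of each gap is the difference between total and direct effect. They show the mechanism and are not an estimate for this trial.

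This should be changed before analysis. It does not undermine the trial, since the unadjusted comparisons are intact.

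**What to change.** 1. In Statistical Analysis, state that the multivariable models adjust only for covariates measured before randomisation, for example the baseline value of the outcome and baseline AHI. Add a graded baseline CPAP measure, such as hours or nights of use, if one is available. Yes/no use at baseline is constant under the inclusion criterion and would adjust for nothing.
2. Add a CPAP-use row to Table 2 with the same time points in both arms, for example within the 6- and 12-month medical evaluation, and report follow-up use descriptively by arm.
3. Amend the limitations paragraph so that any model containing follow-up CPAP use is labelled exploratory and is not presented as the effect of the diet.

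The cost is one table row and one or two sentences. The recording is already intended, and the sample size does not change. The Results section reports recruitment under way and analysis set for February 2026. The change should be dated before that analysis, because choosing between models afterwards would be data-driven.

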### Conclusion

This study seeks to contribute to improving the diet of patients with OSA, thus enhancing the cardiometabolic risk indicators and reducing the patients’ risk of cardiovascular diseases. In addition, we expect to improve the patients’ sleep quality and lifestyle. We consider this intervention will be useful to create a proposal including an MD adapted to Mexican habits that improve the dietary needs of patients with OSA and similarly those of patients with diabetes, obesity, hypertension, and other comorbidities.

## Appendix

Multimedia Appendix 1 SPIRIT guidelines.

Multimedia Appendix 2 Peer review report by the Research Committee of the Hospital Sede Instituto Mexicano del Seguro Social.

## Abbreviations

AHI: apnea-hypopnea index
CPAP: Continuous positive airway pressure
ESS: Epworth Sleepiness Scale
IMSS: Instituto Mexicano del Seguro Social
MD: Mediterranean diet
MEDAS: Mediterranean diet adherence screener
MIMOSA: Mediterranean Diet/Lifestyle Intervention in Obstructive Sleep Apnea
OSA: obstructive sleep apnea
QSQ: Quebec Sleep Questionnaire
SD: standard diet
